# Randomised controlled trial of the Limit of Detection of Troponin and ECG Discharge (LoDED) strategy versus usual care in adult patients with chest pain attending the emergency department: study protocol

**DOI:** 10.1136/bmjopen-2018-025339

**Published:** 2018-10-02

**Keywords:** myocardial infarction, ischaemic heart disease, health economics, cardiology, clinical chemistry

## Abstract

**Introduction:**

Observational data suggest a single high-sensitivity troponin blood test taken at emergency department (ED) presentation could be used to rule out major adverse cardiac events (MACE) in 10%–60% of ED patients with chest pain. This is done using an ‘undetectable’ cut-off (the Limit of Detection: LoD). We combined the LoD cut-off with ECG findings to create the LoDED strategy. We aim to establish whether the LoDED strategy works under real-life conditions, when compared with existing strategies, in a way that is cost-effective and acceptable to patients.

**Methods and analysis:**

This is a parallel-group pragmatic randomised controlled trial across UK EDs. Adults presenting to ED with suspected cardiac chest pain will be randomised 1:1. Existing rule-out strategies in current use across study centres, using serial high-sensitivity troponin testing, will be compared with the LoDED strategy. The primary outcome is successful early discharge (discharge from hospital within 4 hours of arrival) without MACE occurring within 30 days. Secondary outcomes include initial length of hospital stay; comparative costs; patient satisfaction and acceptability to patients. To detect a 9% difference between the early discharge rates (assuming an 8% rate in the standard care group) with 90% power, 594 patients need to be recruited, assuming a 95% follow-up rate.

**Ethics and dissemination:**

The study has been approved by the Frenchay Research Ethics Committee (reference 18/SW/0038). Results will be published in an international peer-reviewed journal. Lay summaries will be made available to patients.

**Trial registration number:**

ISRCTN86184521; Pre-results.

Strengths and limitations of this studyThe safety of the LoDED strategy, using a single high-sensitivity troponin blood test to rapidly exclude acute myocardial infarction, is supported by extensive observational research.This pragmatic multicentre randomised controlled parallel group trial is designed to detect a meaningful improvement in the rate of safe early emergency department discharge using the LoDED strategy, when compared with usual care.Sites will use a variety of usual care pathways and high-sensitivity troponin assays to enhance the generalisability of the findings.Although blinding of clinicians and patients will not be possible, participants will be randomised before troponin results are known to the treating clinician and those performing the outcome assessment data analysis will be blinded.We will undertake an integrated qualitative study to examine patient satisfaction.

## Introduction

The number of patients attending emergency departments (ED) across England and Wales continues to rise, with over 22 million attendances in 2014.^1^ Chest pain makes up nearly 10% of ED attendances and is the most common reason for emergency hospital admission.^2^ The majority of patients with chest pain have prolonged hospital stays during which they undergo testing to rule out acute myocardial infarction (AMI), yet 90% of patients are found to have a benign cause of chest pain, such as gastro-oesophageal reflux.^2^ Prolonged assessment leads to increased National Health Service (NHS) costs, patient anxiety and ED crowding.^3^

The need for prolonged assessment is driven by limitations in current diagnostic strategies. Clinicians rely on three elements to rule out AMI: patient history, ECG and blood test biomarkers. Patient history is an unreliable predictor of AMI,^4^ and few patients (14%) have an ECG that is diagnostic.^2^ Therefore, the majority of patients require biomarker testing. The current biomarker used to rule out AMI is troponin, a protein released into the blood when myocardial injury occurs. Highly sensitive troponin (hs-troponin) assays have been developed recently, meaning that very low concentrations can be measured.^5^ This has led to improved diagnostic accuracy earlier after chest pain onset.^6^ Current consensus guidelines recommend that rule-out hs-troponin testing can be undertaken using two samples taken at presentation and 1–3 hours later.^7 8^ Due to limitations in clinical and laboratory processing times, with strategies reliant on two blood tests, most patients are not discharged until at least 4 hours after ED attendance.^9^ A substantial proportion of patients could potentially be discharged much earlier with a single hs-troponin test taken at presentation to the ED.^10^

It has been proposed that a single hs-troponin test at presentation to the ED could be used to rule out AMI in 9%–60% of patients with very high diagnostic accuracy,^11–17^ using an ‘undetectable’ cut-off for ruling out AMI. This undetectable cut-off is called the Limit of Detection (LoD; lowest analyte concentration at which detection is feasible). Current data supporting the LoD cut-off are from observational studies and in patients who were not actually discharged based on hs-troponin results. Evaluating new diagnostic technologies with observational research alone has important limitations. It is possible that beneficial effects will be diluted because clinicians do not abide by their recommendations.^18^ Furthermore, unanticipated effects such as rebound overuse of resources have previously been reported and have meant that apparently safe strategies are not cost-effective.^19^ Therefore, the clinical and cost-effectiveness of the LoD cut-off remains unknown.

There are two hs-troponin assays currently approved by the National Institute for Health and Care Excellence (NICE): Roche hs-troponin T and Abbott hs-troponin I.^7^ The majority of centres within the Limit of Detection of Troponin and ECG Discharge (LoDED) study use the Roche hs-troponin T assay, reflecting current UK practice (information from manufacturer). The LoD for this assay is <5 ng/L. Some centres use the Abbott hs-troponin I assay with LoD of <2 ng/L. In addition, an emerging hs-troponin I assay (Beckman Coulter Access hs-troponin I) meets criteria to be defined as a high-sensitivity assay but is yet to be evaluated by NICE.^20^ Similarly, the LoD for this assay is <2 ng/L. Performance of all three assays at the LoD appears similar, with similar proportions of patients being eligible for safe early discharge.^15–17 21^ The LoD alone does not have the required diagnostic accuracy for clinical implementation.^13^ However, combining the LoD with ECG findings improves diagnostic accuracy (the LoDED strategy). In a meta-analysis of over 9000 patients evaluating the LoDED strategy with hs-troponin T, pooled sensitivity for 30-day major adverse cardiac events (MACE) was 98.0% (95% CI 94.7% to 99.3%), with 30% of patients eligible for early discharge.^16^ For the Abbott hs-troponin I assay, an analysis of 3155 patients showed a pooled sensitivity for MACE of 97.9% (95% CI 95.4% to 99.2%), with 25% of patients eligible for discharge.^15^ For the Beckman hs-troponin I assay, sensitivity for the rule-out of AMI has been shown to be >99%, in an analysis of 1871 patients, with 34% of patients eligible for discharge.^17^ These data demonstrate the efficacy (safety) of the LoDED strategy, yet they are all from observational cohort studies, where no patient was discharged based on their recommendations; therefore, the clinical effectiveness of the LoDED strategy across populations remains unknown.

The 2016 update to the NICE ‘chest pain of recent onset’ guidelines also supports the use of hs-troponin with a cut-off at the LoD. However, the strategy recommended by NICE requires that the LoD cut-off be combined with a risk score,^22^ such as the Thrombolysis in Myocardial Infarction (TIMI) score,^23^ rather than a normal ECG as we propose in the LoDED strategy. External validation of the NICE approach demonstrated that approximately 15% of patients will be suitable for early discharge, in contrast to approximately 30% using the LoDED strategy.^21^

The LoDED strategy is a straightforward diagnostic tool and current observational evidence suggests it is safe for implementation. The question this trial will answer is whether the LoDED strategy works when implemented in practice, with clinicians actually discharging patients early in significant numbers, without rebound increases in downstream costs and in a way that is acceptable to patients.

## Methods and analysis

### Study design and conduct

This is a pragmatic, multicentre, randomised controlled parallel group trial in adult patients presenting to the ED with suspected cardiac chest pain and who trigger the chest pain investigation pathway. Five hundred and ninety-four participants will be randomised in a 1:1 ratio to be managed according to the LoDED strategy (allowing discharge after a single hs-troponin test at presentation to ED if a participant has no new ischaemic ECG changes and the hs-troponin is below the LoD) or the usual care rule-out strategy in current clinical use at each study site. Usual care will usually include two hs-troponin blood tests taken between 1 and 6 hours after presentation and may vary between sites.

This is an open study. Participants’ study allocations will only be blinded to those performing central review of data for the assessment of outcomes and the statistician analysing the results. All patients will be consented and randomised before their initial hs-troponin results are known. Patients will be ineligible to participate in the trial once the initial hs-troponin result is known to the treating clinician in order to prevent selection bias. The decision to discharge a patient will be made after clinical assessment by the treating clinician. In the event of ongoing clinical concern, the clinician may proceed with further testing and/or admission at their discretion, and contrary to the allocated strategy. Information on protocol adherence will be collected to facilitate a per-protocol analysis as well as the primary intention-to-treat analysis.

The key objective of this study is to conduct a randomised controlled trial (RCT) of the LoDED strategy versus usual care to compare the proportion of patients successfully discharged within 4 hours of arrival, with no MACE during the following 30 days. We will also measure admission rates, hospital bed usage, length of stay, resource use and patient satisfaction, facilitating a health economic evaluation, and determine whether the LoDED strategy is acceptable to patients through qualitative interviews.

Day-to-day trial management is administered through the UKCRC-registered Peninsula Clinical Trials Unit (CTU) at Plymouth University and sponsored by North Bristol NHS Trust.

### Participant flow

Participant flow is summarised in the LoDED trial flow diagram (figure 1).

**Figure 1 F1:**
[figure not shown]
Limit of Detection of Troponin and ECG Discharge (LoDED) trial flow diagram.

### Study population and setting

Participants will be recruited from adult (aged 18 and over) patients attending these EDs with chest pain who trigger the cardiac chest pain investigation pathway, that is, the treating clinician intends to perform investigations to rule out a cardiac cause. Full inclusion and exclusion criteria for the trial are detailed in box 1. The trial will run from 1 December 2017 until 1 December 2019. Recruitment for the trial has commenced (4 June 2018).Box 1Limit of Detection of Troponin and ECG Discharge (LoDED) trial inclusion and exclusion criteriaInclusion criteriaAge ≥18 years.Presenting to the emergency department (ED) with chest pain and triggering the chest pain investigation pathway, that is, the treating clinician intends to perform investigations to rule out a cardiac cause.Peak symptoms occurred <6 hours prior to presentation to the ED.Exclusion criteriaST-elevation myocardial infarction or ischaemic ECG (new T wave inversion >3 mm or ST depression >1 mm) as judged by the treating clinician.Clear non-acute coronary syndrome (ACS) cause for chest pain found at presentation (eg, pulmonary embolism, pneumonia, aortic dissection).Initial hs-troponin result known to the treating clinician.Hospital admission indicated due to other medical/social reasons.Chest pain due to arrhythmia (new-onset atrial fibrillation, atrial flutter, sustained supraventricular tachycardia, second-degree or complete heart block, or sustained or recurrent ventricular arrhythmias).Unable to provide written informed consent (lacks capacity).Unwilling to provide written informed consent.Pain too severe to provide written informed consent.Follow-up will be impossible, for example, lives abroad or no fixed abode.Previous inclusion in the study.Prisoners.Pregnancy.Pre-existing renal failure requiring dialysis.

### Screening, recruitment and consent

Patient screening and recruitment, delivery of the intervention and recording of outcomes will all be carried out within participating UK NHS EDs. Potentially eligible patients will be identified at the time of arrival in the ED by clinical staff or research nurses. During triage or initial assessment the patient will be given the written study participant information sheet (PIS) by a member of the ED clinical team or research nurse. This may be before the chest pain investigation pathway has been triggered, so that a number of patients who have been given the PIS to read may subsequently be ineligible to enter the study. Due to the time taken for laboratory processing of blood samples (>60 min after presentation) and time waiting to be assessed by a doctor, it is anticipated that eligible participants will have over 1 hour to consider the PIS prior to being approached for consent.

Patients will be screened for inclusion in the study by clinical staff or research nurses, and fulfilment of initial eligibility criteria will be recorded on a study-specific screening form. The written consent process will be undertaken by an appropriately trained (Good Clinical Practice; GCP) attending clinician or an appropriate member of the research team depending on individual circumstances.

Once any questions have been answered satisfactorily, patients who are eligible and willing to participate in the study will be asked to complete and sign a consent form, which will be countersigned by the staff member receiving consent. A record of the patient’s consent to participate will be documented in the patient’s ED records, using a pre-prepared sticker. A copy of the completed consent form should be provided to the patient, a copy filed in the investigator site file and a further copy will be filed with a copy of the study PIS in the participant’s ED records.

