### Randomisation

After written consent has been obtained, participants will be randomised to be evaluated using either the existing rule-out strategy used in study centres (control) or the LoDED strategy (intervention) in a 1:1 ratio. The CTU, in conjunction with the study statistician, will provide web-based randomisation, stratified by centre and minimised by age and gender.

To randomise a participant, the recruiting doctor, ED nurse or research nurse will access the secure website and enter brief participant details (initials, date of birth, gender, study site). Once the randomisation process is complete, the computer screen will indicate which diagnostic strategy to follow, including details of the local rule-out strategy for control participants as a reminder for site staff. A printout of the allocation generated by the randomisation website will be taken and filed in the participant’s ED records.

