### Outcomes

#### Primary outcome

The primary outcome is successful early discharge, defined as discharge from hospital within 4 hours of ED arrival, without MACE occurring within 30 days.

The safety endpoint of MACE occurring within 30 days, included within the primary outcome, will be defined as cardiac death, AMI or emergency revascularisation occurring within 30 days of ED attendance (including the index presentation). AMI will be defined according to the universal definition, which states that a rise and/or fall of troponin above the 99th percentile value confirms the diagnosis.^25^ A significant rise and/or fall will be defined as an absolute change in troponin over time of at least half the 99th percentile value of the assay in clinical use.^26^

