### Data analysis

All analyses will be conducted blind to group allocation. A Consolidated Standards of Reporting Trials diagram will be used to report the number of patients screened, recruited and randomised.^27^ It will also detail the number allocated to each group and the frequency of the primary outcome.

The primary outcome of discharge within 4 hours will be analysed by logistic regression using all those randomised in an intention-to-diagnose analysis. The analysis will be stratified by centre to allow for differences between the proportions discharged within 4 hours in the control group at each of the study sites. Heterogeneity of the odds of early discharge at each centre will be investigated and only pooled if appropriate. The OR of early discharge controlling for age, sex and centre will be presented with a 95% CI for each centre individually and combined across centres. In the event of significant heterogeneity in the control group but homogeneity within the intervention group the results will be presented as the rate of early discharge in the intervention group together with 95% CIs. Adherence to the allocated rule-out strategy will be presented as percentage with 95% CIs.

The analysis of the quantitative secondary outcomes will also control for age, sex and centre, with a multiple regression analysis and difference in means reported for the comparison of length of hospital stay between groups and for the total score from the patient satisfaction survey obtained from summing the individual items. The responses for the individual items of the patient satisfaction survey will also be reported by group, but an adjusted analysis will not be carried out.

The incidence of MACE occurring within 30 days of ED attendance in those discharged according to the LoDED strategy versus usual care will also be reported with 95% CIs. As the event rate is expected to be low, it is unlikely to be possible to carry out an adjusted analysis. There are no preplanned interim analyses. A secondary per-protocol analysis will also be performed for the primary outcome.

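### Optional improvement: adjusting for time from ED arrival to randomisation would probably add a little power to the 4-hour primary outcome; leaving it out is not an error

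*Protocol article*

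**What the plan says.** - **Outcome clock.** Under Primary outcome, success is "discharge from hospital within 4 hours of ED arrival, without MACE occurring within 30 days". The clock starts at arrival, not at randomisation.
- **Time before consent.** Under Screening, recruitment and consent, the information sheet is handed over at triage or initial assessment, and "it is anticipated that eligible participants will have over 1 hour to consider the PIS prior to being approached for consent". The reasons given are laboratory turnaround and the wait for a doctor. No mean, spread or maximum is stated.
- **Order of events.** The Randomisation section states "After written consent has been obtained, participants will be randomised". Study design and conduct sets a limit on lateness: "All patients will be consented and randomised before their initial hs-troponin results are known".
- **Balance at randomisation.** The method is "web-based randomisation, stratified by centre and minimised by age and gender".
- **Primary model.** Under Data analysis: "The primary outcome of discharge within 4 hours will be analysed by logistic regression using all those randomised in an intention-to-diagnose analysis". The adjustment set is stated outright: "The OR of early discharge controlling for age, sex and centre will be presented with a 95% CI".

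**The concern.** Time to discharge, measured from arrival, is the sum of the interval before randomisation and the time that remains. The first part is fixed before allocation, so the allocated strategy cannot alter it and it is a legitimate baseline covariate. With an expected hour or more gone, at least a quarter of the 4-hour window (1/4 = 25%) has usually been used before allocation can have any effect.

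The interval could matter because the margin is thin. The Sample size section expects participants below the LoD to leave at a median of 3.5 hours, only half an hour inside the cut-off. Waits for a doctor and for the laboratory plausibly vary from hour to hour within a site as well as between sites, so the centre term would capture only part of the variation.

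At stake is a small amount of power that could be had almost free, not the validity of the comparison.

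**Working it through.** **1. The plan's own figure.** Inputs from Sample size: 8% v 17%, 90% power, 5% significance (taken as two-sided), 95% follow-up. With mean proportion 0.125:

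n = [1.960 × √(2 × 0.125 × 0.875) + 1.282 × √(0.08 × 0.92 + 0.17 × 0.83)]² / 0.09² = 281.7, so 282 per group and 564 in total. Then 564/0.95 = 593.7, so 594. The stated figures reproduce without any covariate.

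**2. Reference point for the logistic model.** The log odds ratio is ln[(0.17 × 0.92)/(0.08 × 0.83)] = ln 2.36. Its standard error is √[1/(282 × 0.08 × 0.92) + 1/(282 × 0.17 × 0.83)] = 0.271. So z = 3.16 and Wald power is 88.6%. The difference from 90% reflects the approximation used, not a fault in the plan.

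**3. Adding the interval, analytic.** The article gives neither the spread of the delay nor its effect, so both are assumptions here. The delay is 1 h plus a gamma variable with the SD shown. The odds ratio of early discharge per extra hour of delay is 0.7 (weak) or 0.2 (strong). Marginal rates are held at 8% and 17%. The last column is the variance of a risk difference adjusted for the interval relative to the unadjusted one, that is, {2E[p₀(1−p₀)] + 2E[p₁(1−p₁)] + Var(p₁−p₀)} / {2(0.08 × 0.92 + 0.17 × 0.83)}, where p₀ and p₁ are the success probabilities given the delay.

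| SD of delay | OR per hour | SE of log OR | z | Power | Variance ratio |
|---|---|---|---|---|---|
| not adjusted | – | 0.271 | 3.16 | 88.6% | 1 |
| 0.25 h | 0.7 | 0.271 | 3.17 | 88.6% | 0.999 |
| 0.25 h | 0.2 | 0.273 | 3.19 | 89.0% | 0.987 |
| 0.5 h | 0.7 | 0.271 | 3.17 | 88.7% | 0.997 |
| 0.5 h | 0.2 | 0.277 | 3.24 | 89.9% | 0.956 |
| 0.75 h | 0.7 | 0.272 | 3.17 | 88.8% | 0.994 |
| 0.75 h | 0.2 | 0.283 | 3.30 | 91.0% | 0.917 |
| 1.0 h | 0.2 | 0.290 | 3.38 | 92.3% | 0.872 |

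Up to an SD of 0.75 h the gain is 0 to 2.4 points of power (91.0 − 88.6), or up to about 9% in effective sample size (1/0.917 = 1.09). The last row (3.7 points; 1/0.872 = 1.15) is an extreme, since randomisation has to come before the troponin result is known.

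The standard error of the log odds ratio never falls. The test statistic rises because the conditional odds ratio moves away from 1, from 2.36 to 2.54 at SD 0.75 h and OR 0.2 per hour.

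**4. Simulation of the same delay model** (1,500 trials per setting, 282 per arm). At SD 0.25 h there was no difference beyond simulation noise. At SD 0.5 h the gain was at most 0.7 points (91.3% to 91.9% in rounded figures). At SD 0.75 h power went from 90.3% to 92.1% (OR 0.3 per hour) and from 90.7% to 92.9% (OR 0.2). With the weak effect there was no gain.

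**5. A different delay model.** Here the interval was lognormal (median 1.25 to 2.0 h, log-SD 0.3 to 0.45), the remaining time lognormal (log-SD 0.5), with 30% below the LoD and rates calibrated to 8% and 17%. In 2,000 trials per scenario, effective-sample ratios were 1.019 to 1.073 and power rose by 0.4 to 1.4 points.

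**6. Closer to the planned model.** With centre in the model and randomisation forced before the troponin result, effective-sample ratios were about 1.02 to 1.12 and power changed by about 0 to +3 points. When randomisation timing was unrelated to patient flow, the ratio was 1.00. Adjusting did no harm.

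**The case against.** The strongest reply is that the plan contains no mistake here. It adjusts for exactly the factors used in randomisation, which is coherent and conventional. Randomisation balances the interval in expectation, and the confidence interval already allows for chance imbalance. This stands in full and is why the point is only a suggestion.

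A reader might infer more than the documents support, in three ways.

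- **That precision is being lost.** For a logistic odds ratio this is wrong: the standard error stays the same or grows on adjustment. The benefit is in power, or in a narrower interval for a standardised risk difference.
- **That someone randomised late has almost no chance of success in either arm.** The article gives no data on this. Even the model in step 5 leaves 2% to 9% success in the LoDED arm at the 90th percentile of the interval.
- **That long delays are common.** A median discharge of 3.5 h including 60 minutes for the decision implies a troponin result near 2.5 h, and randomisation must precede knowledge of it. A lognormal delay with median 2.0 h and log-SD 0.45 puts 31% of participants beyond 2.5 h, so the upper scenarios of step 5 fit the protocol poorly.

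It is also fair to say that steps 3 to 5 compare with a model holding arm alone, whereas the planned model includes centre, which may absorb between-site delay. Step 6 answers this in part: with centre included and delay bounded, a gain remains unless timing reflects only such things as staff availability.

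**Conclusion.** This is an optional, nearly free improvement. The sequence is clear in the text: the clock starts at arrival, allocation is expected more than an hour later, and the interval is absent from a stated adjustment set. Omitting it causes no bias and leaves 282/564/594 intact.

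Including it would probably add about 0 to 3 points of power, or 0% to 12% in effective sample size. That range rests wholly on assumed delay distributions and assumed effects of delay. It reaches zero if randomisation timing is unrelated to patient flow. For length of stay, a linear model, adjusting for a baseline component of the stay should reduce residual variance, but no size was calculated.

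**What to change.** In Data analysis, before unblinding, extend the control set to *age, sex, centre and time from ED arrival to randomisation (continuous)* for the primary logistic regression, and use the same set in the length-of-stay regression. Recruitment has begun, but the change affects neither recruitment nor care. With blinded analysis and no planned interim analyses, it can still be prespecified.

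Costs:

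- One more parameter against about 70 expected successes (0.08 × 282 + 0.17 × 282 = 22.6 + 47.9 = 70.5).
- The reported odds ratio becomes conditional on the interval, so it lies further from 1 and its standard error does not shrink. The text should say so. If the gain is to show as a narrower interval, a standardised risk difference from the same model would show it.
- Arrival time is needed for the outcome anyway. That the web system records the time of allocation is an assumption: the Randomisation section lists only initials, date of birth, gender and site as entered. This should be confirmed first.
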